### Outcome measures

The primary outcome of the study is the patient-reported outcome (PRO) *quality of recovery* on postoperative day 1 (24 h after surgery) measured with the validated Dutch version of the QoR-40 questionnaire. This survey consists of 40 short questions across five domains: physical comfort (e.g., nausea, dizziness or shivering), emotional state (general well-being, feeling anxious or angry), physical independence (ability to wash and groom), psychological support (from hospital staff, family and friends), and pain (presence of moderate pain, severe pain, and pain in several locations). Patients rate these aspects of recovery on a scale of 1 to 5, resulting in a total score between 40 and 200. Separate scores on each subdomain will also be explored. When the clinical condition of the patient allows it, they self-complete the questionnaires. If this is not the case, they will be assisted by a nurse blinded to the treatment allocation.

Intraoperative secondary outcome measures are quality of the surgical field quantified on the L-SRS every 15 min, estimated blood loss, pulmonary mean driving pressure, and intraoperative complications. Table 2 shows an overview of questionnaires and parameters collected at the post anesthesia care unit (PACU), surgical ward, and after discharge. Postoperative secondary outcomes are quality of recovery measured with the QoR-40 questionnaire after 72 h and 1 week; pain scores; postoperative nausea and vomiting (PONV); use of analgesics and anti-emetics after 1, 8, 24, and 72 h; intra-operative and postoperative complications up to 3 months after surgery (classified by the CLASS-Intra [25] and Clavien-Dindo [26] classifications, respectively); and length of hospital stay and time to reach discharge criteria. If patients are discharged before completion of the QoR-40 after 72 h or 1 week, the questionnaires are taken home and returned to the researchers by post. Pain is scored on a scale of 0–10 in rest and upon movement, if pain is acceptable yes or no and if shoulder pain is present yes or no. Nausea is scored on a scale of 0–10. Discharge criteria are as follows: adequate pain relief with oral analgesics, passage of flatus or defecation, intake of solid foods is tolerated, patient is capable of independent mobilization, and patient accepts discharge. The actual date of hospital discharge is also registered. Pain, nausea, and discharge criteria are scored by the ward nurse responsible for the clinical care of the patient, who is also blinded to the treatment allocation. Postoperative complications are extracted from the electronic patient file 1 month after surgery.

**Table 2 Tab2:** Variables and time points

	− 1 day	1 h	8 h	24 h	48 h	72 h	1 week	1 month	3 months

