General anesthesia is maintained with propofol aimed at a bispectral index score of 45–55, remifentanil 0.25–2 mcg/kg/min, a bolus injection of 0.2–1 mg/kg esketamine and a bolus injection of 1–1.5 mg/kg lidocaine 1% followed by continuous infusion of lidocaine 1% at 0.5–3 mg/kg/h. In both groups, the Automated TOF PTC (ATP) function of the TOF scan is used to measure the level of neuromuscular blockade every 5 min throughout the whole surgery. This function automatically determines whether a response to train-of-four stimulation is present and if TOF count or PTC should be measured. In group A (low pressure PNP with deep NMB), continuous infusion of 0.3–0.4 mg/kg rocuronium is initiated directly after intubation and titrated to a PTC of 1–2. If PTC is 0, continuous infusion will be decreased (but not stopped) until a PTC of 1 or 2 is reached. In group B (normal pressure with moderate NMB), a bolus or low dose of continuous rocuronium can be administered after intubation as normally done in clinical practice, titrating towards a TOF count of 1–2. Reaching deep NMB is carefully prevented in this group; if TOF count reaches 0, the infusion of rocuronium will be stopped until neuromuscular function is recovered.

After introduction of the camera trocar, the insufflation pressure of carbon dioxide is set to 8 mmHg in group A and 12 mmHg in group B, out of the surgical team’s sight. After introduction of the last trocar and every 15 min during surgery, a blinded OR nurse will ask the surgeon to rate the surgical conditions on the Leiden-Surgical Rating Scale (L-SRS) as displayed in Table 1. In case of inadequate surgical conditions (at any time during the surgery), defined as < 4 out of 5 points on the L-SRS scale, intra-abdominal pressure will be increased with 2 mmHg to 10 mmHg and a maximum of 12 mmHg in group A or 14 mmHg and a maximum of 16 mmHg in group B, respectively. If the level of NMB is not in the desired range, this will be corrected first. If surgical conditions remain compromised despite the increase in pressure, the surgeon can decide to convert to a hand-assisted or open procedure. All administered medication and intraoperative parameters are documented in the digital anesthesia report in the electronic patient file as in usual clinical practice. At the end of surgery, intraoperative complications will be registered by the surgeon.

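### The L-SRS is both the surgical-field outcome and the trigger for raising pressure, so a comparison over the whole series is attenuated as a measure of the field at 8 versus 12 mmHg

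*Protocol article*

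**What the plan says.** Outcome measures names the "quality of the surgical field quantified on the L-SRS every 15 min" among the intraoperative secondary outcomes, with blood loss, driving pressure and complications. Neither the need for a pressure increase nor the pressure reached is on that list.

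Study protocol sets out how the scale is used during the operation:

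- Starting point: "the insufflation pressure of carbon dioxide is set to 8 mmHg in group A and 12 mmHg in group B".
- Rating schedule: "After introduction of the last trocar and every 15 min during surgery, a blinded OR nurse will ask the surgeon to rate the surgical conditions".
- Trigger: "In case of inadequate surgical conditions (at any time during the surgery), defined as < 4 out of 5 points on the L-SRS scale".
- Action: pressure is "increased with 2 mmHg to 10 mmHg and a maximum of 12 mmHg in group A or 14 mmHg and a maximum of 16 mmHg", the last two figures being those for group B.
- Order of steps: "If the level of NMB is not in the desired range, this will be corrected first".
- If the field stays poor despite the increase, the surgeon may convert.

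Statistical methods and sample size calculation assigns secondary outcomes a t test or a Mann-Whitney test, with all analyses by intention to treat. It states no summary measure for the L-SRS series and no treatment of ratings made after a pressure increase.

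**The concern.** The rating is at once the outcome and the signal that changes the exposure. Patients with a poor field at their allocated pressure are the ones moved to a higher pressure, and they continue to be rated there. If more pressure improves the field, which is the premise of the rule, the worse arm gains more from the rule and the arms move together over the operation.

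The article's rationale is that deep block permits lower pressure without loss of surgical field, and this outcome is the trial's own check of it. Similar L-SRS values over the whole operation could be read as showing an equally good field at 8 mmHg, even if many group A patients were operated on at 10 or 12 mmHg. The listed outcomes contain no escalation measure that would show this.

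**Working it through.** The article gives no planned difference, SD or power for the L-SRS, so there is no figure to reproduce; its sample size calculation concerns the QoR-40 only.

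**Step 1. The pressure contrast under the rule.** Against a group B patient still at 12 mmHg, a group A patient differs by 12 − 8 = 4 mmHg at the start, 12 − 10 = 2 mmHg after one step, and 12 − 12 = 0 mmHg after two. Group B patients can also be raised, to 14 and 16 mmHg.

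**Step 2. Complete rescue.** Assumptions:

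- 22% of group A score 3 at the first rating. The figure is borrowed from the Background, where a cited colorectal study completed 78% of operations at 8 mmHg (100 − 78 = 22).
- 5% of group B score 3 at the first rating.
- Adequate fields score 4 (30%) or 5 (70%), mean 0.3 × 4 + 0.7 × 5 = 4.7.
- An inadequate field lasts one rating (70%) or two (30%), mean 0.7 × 1 + 0.3 × 2 = 1.3 ratings, and is then fully restored.

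First-rating difference = (0.22 − 0.05) × (4.7 − 3) = 0.289. Difference in whole-operation means with k ratings = 0.289 × 1.3 / k:

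| k | Difference in means | Share lost, 1 − 1.3/k |
|---|---|---|
| 8 | 0.047 | 84% |
| 10 | 0.038 | 87% |
| 13 | 0.029 | 90% |

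A simulation of 40,000 patients per arm gave 0.047, 0.037 and 0.029. The share lost depends only on the assumed rescue time and number of ratings.

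**Step 3. Partial rescue.** A second simulation, also 40,000 per arm, used 10 ratings on the 1–5 scale, patient SD 0.5, rating SD 0.35 and an underlying mean of 4.65 in group B. Each score below 4 gave +2 mmHg, at most twice, in both arms. All L-SRS values are assumed; block correction and conversion were not modelled. Entries are the difference (B − A) in the mean of all ratings, with the share lost:

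| Underlying mean, group A | Without the rule | 0.1 points per mmHg | 0.25 points per mmHg | 0.5 points per mmHg |
|---|---|---|---|---|
| 4.3 | 0.29 | 0.26 (10%) | 0.22 (24%) | 0.17 (41%) |
| 4.0 | 0.57–0.58 | 0.49 (16%) | 0.39 (33%) | 0.27 (53%) |
| 3.7 | 0.87 | 0.71 (18%) | 0.54 (38%) | 0.35 (60%) |

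For example, 1 − 0.49/0.58 = 16%. The difference stays above zero in every cell.

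**Step 4. What the rule leaves intact.** In the middle row the first-rating difference is 0.57–0.58 with or without the rule, and the lowest-rating difference moves only from 0.64–0.65 to 0.61–0.62. The share of patients ever below 4 is 53% versus 13% either way, because in the simulation a patient's first low score comes before any step. The last rating suffers most: 0.57–0.58 falls to 0.44, 0.31 or 0.16.

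**The case against.** The strongest reply is that the article states how often ratings are taken, not how they are summarised. A first rating, a lowest rating or a share below 4 would all fit the text, and that choice is commonly left to the full protocol or the SAP. This stands against two stronger readings. A reader might infer that all ratings are pooled or averaged, or that the t or Mann-Whitney test is applied to individual ratings as if they were independent. The article says neither, and with one value per patient those tests are not invalidated by within-patient correlation.

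A reader might also infer that the rule erases the difference. The documents do not support that:

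- Out-of-range block is corrected before pressure is raised, so a score below 4 does not always lead to a step.
- Increases are capped, and the field may stay poor after them.
- Group B is escalated by the same rule.
- Differences between scores 4 and 5 trigger nothing.
- Low scores given at a scheduled rating stay in the series.

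The 83–90% losses come from assuming complete rescue within one or two ratings. The 22% is the share of operations not completed at low pressure in another study that titrated pressure individually; it is not a first-rating failure rate.

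Finally, under intention to treat, the field under the whole strategy, escalation included, is a legitimate target. Later ratings also carry information, since the Discussion says that maintaining deep block throughout is difficult. This stands too, and is why the series should be kept. It does not make that target answer the question of 8 versus 12 mmHg, and the article does not say which of the two it means.

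**Conclusion.** The concern holds as attenuation. The article itself fixes both the repeated outcome and a rule acting on that same score, without separating ratings before and after an increase and without listing escalation as an outcome. As a measure of the field at 8 versus 12 mmHg, a comparison over the whole series is pulled towards no difference, provided that raising pressure improves the field.

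The size cannot be derived from the documents. It was about 10–60% with partial rescue and 83–90% with complete rescue, so roughly 10–90% across assumed scenarios. The outcome is secondary, and the primary QoR-40 analysis is not affected by this route.

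**What to change.** Change the analysis only; the clinical rule stays as written.

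1. Add as surgical-field outcomes the proportion of patients with any pressure increase and the highest pressure reached, by group.
2. Report the L-SRS before any increase: the first rating after the last trocar, or the share of patients ever scoring below 4. State how a patient is handled whose pressure was raised before that first rating, and record any low score given between scheduled ratings, since the rule applies throughout surgery.
3. Keep all ratings, either as one summary value per patient or in a model with a patient random effect, and label the result as conditions under the strategy with rescue.

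The cost is a few lines of analysis text plus extraction of the pressure steps from the intraoperative record. The article says that intraoperative parameters are documented but does not name these steps, so their availability should be confirmed. The statistical drawback is that a first or pre-increase rating is noisier than a whole-operation mean.

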**Clinical parameters**									
Pain scores and PONV	X	X	X	X		X			
Analgesia and anti-emetics	X	X	X	X		X			
Complications				X	X	X	X	X	X
Discharge criteria			X	X	X	X			

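### Pain and nausea at 72 h are scored by the ward nurse and have no stated route home, so patients discharged earlier would drop out of that comparison

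*Protocol article*

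**What the plan says.** All of the following is in the protocol article, under Outcome measures and in Table 2.

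- **Time points.** Pain and postoperative nausea and vomiting (PONV) are secondary outcomes, followed in the same list by "use of analgesics and anti-emetics after 1, 8, 24, and 72 h". In Table 2 the rows "Pain scores and PONV" and "Analgesia and anti-emetics" are both marked at 72 h.
- **Content.** Pain is rated 0–10 at rest and on movement, with yes/no items for acceptability and shoulder pain. Nausea is rated 0–10.
- **Scorer.** "Pain, nausea, and discharge criteria are scored by the ward nurse responsible for the clinical care of the patient". No other scorer is named for pain or nausea.
- **Early discharge.** "If patients are discharged before completion of the QoR-40 after 72 h or 1 week, the questionnaires are taken home" and then posted back. No such route is stated for pain or nausea.
- **Discharge criteria.** These include "adequate pain relief with oral analgesics, passage of flatus or defecation, intake of solid foods is tolerated", together with independent mobilization and the patient's acceptance of discharge. Table 2 checks them at 8, 24, 48 and 72 h.

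Under Statistical methods and sample size calculation, secondary outcomes are compared by t test, Mann-Whitney U test or chi-square test, and every analysis is declared to be by intention to treat.

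**The concern.** The ward nurse no longer has the patient after discharge. If that nurse is the source of the 72 h scores, the scores exist only for patients still in hospital. Who remains is not a random subset: adequate pain relief is itself a discharge criterion, and the other criteria track recovery. If the trial's hypothesis is right and group A recovers faster, its better recoverers leave the 72 h sample first and in greater number.

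The planned tests would then compare slower recoverers in one arm with a differently selected set of slower recoverers in the other. That is not an intention-to-treat comparison. The likely direction is against the arm that recovers faster, so a real reduction in pain or nausea would look smaller, with fewer patients to show it.

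**Working it through.** **1. The plan's own figure.** The only stated calculation concerns the primary outcome. With a difference of 6.3, SD 15, two-sided alpha 5% and 80% power, n = 2 × (1.960 + 0.842)² × 15² / 6.3² = 89 per group, as stated. The total of 204 matches 178 × 1.15 = 204.7 (178 / 0.85 would give 210). This rests on the 24 h QoR-40 and is untouched by the present point. No figure is given for 72 h pain or nausea, or for the share of patients home by then, so everything below is illustration under assumptions.

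**2. Discharge by a recovery threshold.** Assumptions:

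- Slow recovery S is standard normal in group B and shifted by −0.42 SD in group A (6.3/15, borrowed from the primary outcome).
- Patients with S below a cut c are home before 72 h.
- 72 h pain (SD 1) has correlation ρ with S, and the true pain effect is −0.42 SD.

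With λ(c) = φ(c) / [1 − Φ(c)], the bias among inpatients is ρ × [λ(c + 0.42) − λ(c)].

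| Home before 72 h, B / A | ρ | λ(c), λ(c + 0.42) | Bias (SD) | Seen instead of −0.42 | Attenuation |
|---|---|---|---|---|---|
| 10% / 19% | 0.3 | 0.195, 0.342 | +0.044 | −0.376 | 10% |
| 10% / 19% | 0.5 | 0.195, 0.342 | +0.073 | −0.347 | 17% |
| 50% / 66% | 0.3 | 0.798, 1.083 | +0.086 | −0.334 | 20% |
| 50% / 66% | 0.5 | 0.798, 1.083 | +0.143 | −0.277 | 34% |

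A simulation of the same model gives −0.38 to −0.27, which is up to 36% if taken from the rounded values. If recovery differs but the true pain effect is zero, the bias column is the false difference against group A.

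Precision, from 102 patients per arm:

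- All patients scored: 0.42 / √(2/102) = 3.00, so power is Φ(3.00 − 1.96) = 85%.
- First row: 92 (B) and 82 (A) remain and the SD among them is about 0.98. The ratio is 0.376 / 0.149 = 2.52, so power is 71%.
- Last row: 51 (B) and 34 (A) remain and the SD is about 0.91. The ratio is 0.277 / 0.201 = 1.38, so power is 28%.

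**3. Discharge that depends gradually on pain itself.** The probability of being home is logistic(base − slope × z), where z is pain in SD units, base runs from −0.5 to 0.5 and slope from 0.8 to 1.2 (39% to 61% of group B home). The mean of z among those who stay is ∫z s(z)f(z)dz / ∫s(z)f(z)dz, where s = 1 − logistic(base − slope × z) and f is the normal density of z in that arm. Integrating numerically for shifts of 0.25 and 0.40 SD gives attenuation of 12% to 23%.

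**4. Discharge that depends gradually on recovery, with pain only correlated.** The form is as in step 3, with slope 1.0, shift 0.40 SD, ρ 0.3 to 0.5 and 13% to 60% of group B home. Attenuation is 3% to 9%. This may be closer to the text, since only one of the five discharge criteria concerns pain.

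**5. Limits.** With no discharge before 72 h the bias is zero in every model. If neither recovery nor pain differs between arms there is no bias, only loss of precision.

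**The case against.** The strongest reply is that the article is silent here rather than wrong. It condenses a fuller protocol that is not shown. Table 2 is introduced as covering collection in recovery, on the ward and after discharge. The ward-nurse sentence also serves to describe assessor blinding and may not list every source, since pain and PONV are also marked at 1 h, when the patient may still be in the recovery unit. This has some weight, but it does not dispose of the point. The mention of collection after discharge is accounted for by the posted QoR-40, the 3-month questionnaires and the complications. It does not override the specific sentence on who scores pain and nausea, set beside a home route for one instrument only.

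A second reply stands in part. The QoR-40 that goes home has a pain domain, and a physical comfort domain that includes nausea, and its subdomain scores are to be explored. Time to discharge criteria and the actual discharge date are also recorded. So 72 h symptoms are not wholly lost, and faster recovery would show elsewhere. These do not replace the 0–10 ratings or the acceptability and shoulder-pain items.

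A reader might infer more than the text supports:

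- **That analgesic and anti-emetic use also comes from the ward nurse alone.** The sentence covers pain, nausea and discharge criteria. The source of postoperative medication data after discharge is simply not stated.
- **That many patients will in fact be missing.** The take-home clause covers 72 h or 1 week and gives no rate.

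**Conclusion.** The point holds for 72 h pain and nausea. As written, patients discharged before 72 h would lack these scores, and the comparison would be conditioned on a post-randomisation state linked to the outcome. The likely effect is attenuation of a true benefit in the arm that recovers faster, with loss of precision.

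The size cannot be fixed from the documents. Across the assumed discharge rates and models the attenuation is about 3% to 34%, and the spread reflects the choice of model as much as anything in the plan.

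The reach is narrow: one time point of some secondary outcomes. It would be wrong to infer that the primary outcome, the sample size or the 1, 8 and 24 h scores are compromised. The correction is cheap and worth making, but the trial's main conclusion does not depend on it.

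**What to change.** 1. Add the 72 h items to the QoR-40 form that already goes home and comes back by post: pain at rest and on movement, acceptability, shoulder pain, nausea, and analgesics and anti-emetics taken. State the source of medication use after discharge.
2. Report the number discharged before 72 h in each arm.
3. For patients already discharged without these items, analyse 72 h pain and nausea with a likelihood-based repeated-measures model that uses the 1, 8 and 24 h scores, in place of a test restricted to inpatients. This assumes that the earlier scores explain the absence, and that assumption should be stated.

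The cost is a few lines on an existing form. Home scores are self-rated rather than taken by a nurse, a small difference in mode within the trial, so the mode should be recorded. Inclusion was predicted to end in October 2020 and the article appeared in June 2020, so the new items may reach only the later patients. For the rest, steps 2 and 3 carry the correction.

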**Questionnaires**									
QoR-40	X			X		X	X		
McGill pain	X								X
RAND-36	X								X
**Clinical parameters**									
Pain scores and PONV	X	X	X	X		X			
Analgesia and anti-emetics	X	X	X	X		X			
Complications				X	X	X	X	X	X
Discharge criteria			X	X	X	X			

### Adverse events and reactions

Adverse events are not expected, as the combined components of the intervention have demonstrated to be safe. As illustrated above, the use of deep neuromuscular blockade allows for a safe reduction in intra-abdominal pressure without compromising the surgical field. If surgical conditions are compromised nonetheless, the pressure will be increased to ensure patient safety at all times. The benefits of deep neuromuscular blockade are increasingly recognized in many types of surgery, with some reservation regarding reversal of different types of neuromuscular blocking agents and the risk of residual relaxation [27]. Sugammadex is able to safely reverse prolonged rocuronium-induced deep neuromuscular block, with no recurrence of blockade [28, 29]. To prevent an increased risk of pulmonary complications, neuromuscular monitoring will strictly be applied as specified in the ERAS Society Recommendations for perioperative care in elective colorectal surgery [30]. A recent retrospective study by Boon and colleagues even shows that compared to low dose, high-dose rocuronium is associated with a lower incidence of unplanned 30-day readmissions than low-dose rocuronium [31]. Patients will be observed at the PACU to confirm smooth recovery from anesthesia.

### Statistical methods and sample size calculation

The mean clinically important difference on the QoR-40 questionnaire as described by Myles et al. is 6.3 points on a scale of 40–200, with a standard deviation of 15 points [32]. In order to achieve 80% power to detect a 6.3 point difference with an *α* of 5%, a sample size of 89 patients per group is needed. Considering a 15% conversion rate to open surgery, 204 patients are required to secure 178 patients for the final analysis.

For the primary outcome analysis, factorial ANCOVA will be used to compare the QoR-40 score on postoperative day 1 for groups A and B and adjusted for covariates. For secondary outcome variables, a Student’s *t* test will be used to compare normally distributed variables, and a Mann-Whitney *U* test will be used for skewed variables. For categorical variables, a chi-square test will be performed. A *P* value of < 0.05 will be considered statistically significant. All analyses will be performed on an intention to treat base. For exploratory outcome measures, Bonferroni correction for capitalization on chance will be applied.

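### The sample size counts patients converted to open surgery as lost to the final analysis, which contradicts the intention-to-treat rule in the same section

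*Protocol article*

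**What the plan says.** In the protocol article, *Statistical methods and sample size calculation*, the clinically important QoR-40 difference "is 6.3 points on a scale of 40–200, with a standard deviation of 15 points". The target is 80% power for that difference. At a 5% α the calculation arrives at 89 in each arm, that is, 178 in total. It then adds: "Considering a 15% conversion rate to open surgery, 204 patients are required to secure 178 patients for the final analysis".

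The next paragraph of that section fixes the analysis population: "All analyses will be performed on an intention to treat base".

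The *Study protocol* section places conversion during the operation, at the end of the escalation path: "If surgical conditions remain compromised despite the increase in pressure, the surgeon can decide to convert to a hand-assisted or open procedure". On that path the maximum pressure is 12 mmHg in group A and 16 mmHg in group B.

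**The concern.** The two statements about who is analysed do not fit together. If 204 are randomised so that 178 are left once conversions are allowed for, converted patients are being counted out of the final analysis. Under intention to treat, conversion removes nobody. The article gives no second analysis set, replacement rule or other reconciliation. An analyst could cite one sentence to drop converted patients and the other to keep them, and could choose after seeing the data.

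The choice is not neutral. Conversion follows randomisation and is triggered by poor surgical conditions, which the allocated pressure and depth of block are meant to affect. It may also go with worse recovery on day 1. Excluding on it would compare two groups that randomisation no longer makes alike. Keeping converted patients protects the comparison but may dilute the expected difference, so the stated 80% power, computed for 178 patients with the full effect, does not describe that analysis.

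**Working it through.** **Inputs from the article:** difference 6.3, SD 15, α 5%, power 80%, 1:1 allocation, 15% conversion, 204 randomised, 178 analysed. Sidedness is not stated. Two-sided is assumed because it returns the article's 89 per group (one-sided gives 71).

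**1. Reproducing the plan's figures**
- n per group = 2 × (1.960 + 0.842)² × 15² / 6.3² = 89.0, so 89 (the t-test needs 90). This agrees with the article.
- 178 × 1.15 = 204.7, which is the stated 204 when rounded down. The usual inflation is 178 / 0.85 = 209.4, so 210. Taken literally, 204 × 0.85 = 173.4 patients remain, with power about 79%. This gap is minor and is not the point here.
- What the arithmetic does show is that the 204 − 178 = 26 extra patients are there only to replace conversions.

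**2. Power if all 204 are analysed as randomised**

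Assume 15% conversion in both arms, and let converted patients receive a fraction f of the effect. The expected difference is 6.3 × (0.85 + 0.15f). With 102 per arm the standard error is 15 × √(2/102) = 2.10, and power is approximately Φ(difference / 2.10 − 1.96).

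| f | Expected difference | Power, normal | Power, t-test | n per arm for 80% (normal) |
|---|---|---|---|---|
| 1 | 6.30 | 85.1% | 84.7% | 89 |
| 0.5 | 5.83 | 79.2% | 78.9% | 105 |
| 0 | 5.36 | 72.2% | 71.8% | 124 |

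These figures are for an unadjusted comparison. The planned ANCOVA would do better if its covariates explain variance. The article does not name the covariates. If baseline QoR-40 were one, with an assumed correlation of 0.3 to 0.5 with the day-1 score, the residual SD is 15 × √(1 − r²) and the f = 0 row rises to about 76% to 83%.

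**3. Bias if converted patients are dropped**

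Let pA and pB be the conversion rates, and let converted patients score D points below the others in their arm. Each arm's full mean equals its non-converted mean minus p × D. The difference (A minus B) among non-converted patients therefore equals the intention-to-treat difference plus (pA − pB) × D.
- Assumed 20% in A and 10% in B, D = 10 to 20: shift of +1.0 to +2.0 points in favour of A. The upper end is 2.0 / 6.3 = 32% of the target difference.
- Rates reversed: −1.0 to −2.0 points.
- Equal rates and equal D: zero.

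The split by arm and the value of D are illustrations. The article gives neither.

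**The case against.** The strongest reply is that exclusion is never stated. Conversion is not among the exclusion criteria, nothing in *Study protocol* ends follow-up after it, and the only explicit rule on the analysis population is intention to treat, for all analyses. The 15% can be read as a loose planning margin. This stands in part: a reader might infer that the trial will drop converted patients, and the article does not show that. It does not remove the conflict, because the sample-size sentence speaks of the final analysis itself and gives conversion as its only reason for loss.

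Three further inferences are tempting and go too far.
- *That the trial really has 72% power.* That is the extreme case of no benefit in any converted patient under an unadjusted test. The *Discussion* reports that deep block appears beneficial independently of insufflation pressure, so some effect may persist after conversion. With half the effect, power is about 79%, essentially the planned level.
- *That nothing is left for missing questionnaires.* With everyone kept and no dilution, going from 204 to 178 tolerates 26 / 204 = 12.7% missing day-1 scores at about 80% power. The margin disappears only if converted patients are dropped or dilution is substantial.
- *That group A will convert more often and be flattered by exclusion.* Its pressure ceiling is lower, but it also receives deep block, which the *Background* reports improves surgical conditions (mean L-SRS difference 0.65). The direction is open.

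The full protocol or analysis plan may define the analysis sets. That limits what can be said about the analysis that will be run, but it does not excuse two conflicting statements in one section of the article.

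**Conclusion.** The contradiction is real. The sample-size justification treats conversion as loss from the final analysis, while the same section promises intention to treat. The 89 per group is correct and the 204 is close to it in logic; the fault lies in the reason given for the inflation.

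Two sizes attach to it, both dependent on assumptions. If converted patients are kept, unadjusted power with 204 analysed is about 85%, 79% or 72% for full, half or no effect in the 15% converted, and higher if the ANCOVA covariates explain variance. If they are dropped, the bias can go either way and its size cannot be taken from the documents; the assumed split of 20% versus 10% with a 10 to 20 point deficit gives 1 to 2 points. The documents do not establish that converted patients will be excluded or that the trial is underpowered.

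**What to change.** Before any unblinded analysis, amend the section as follows.
1. State that every randomised patient is analysed in the allocated group, whether or not the operation was converted to a hand-assisted or open procedure.
2. Remove conversion as a reason for loss from the analysis set. Re-justify the 15% as possible effect dilution, as missing day-1 QoR-40 scores, or as a stated mix of the two.
3. Restate power for 204 analysed together with its assumptions: about 85%, 79% and 72% for full, half and no effect in converted patients (unadjusted t-test, SD 15). Note that covariate adjustment may raise these, and give an explicit assumption for missing day-1 scores.
4. Label any analysis without converted patients as a sensitivity analysis only.

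The cost is one paragraph of wording. No new patients or data are needed, but the stated power becomes a range whose lower end is below 80%.
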